**Table 3 Tab3:** **Investigational schedule for patients in group 2 of phase II**

Consultation visit	1	2	3	4	5	6	7	8	9	10	11^1^	12	13	14
Days	(−10) to (−3)	1	3 or 4	5	6	7	8	11	16±2	22±2	29±3	168±14	252±14	336±14
Parameter	Screening^2^	MSC infusion^3^	Tumor resection	GCV infusions^4^										
**Informed consent**	X													
**Inclusion/exclusion criteria**	X													
**Medical history/demography**	X													
**Physical examination**	X										X			
**Adverse events**		X	X	X	X	X	X	X	X	X	X			
**Concomitant medication**	X	X	X	X	X	X	X	X	X	X	X			
**Vital signs**	X	X^5^		X^6^	X^7^	X^7^	X		X		X			
**Body weight**	X	X^8^		X^9^			X		X		X			
**12-lead ECG**	X						X				X			
**Cardiac monitoring**		X^10^		X^11^	X^12^									
**Oxygen saturation**		X^13^		X^11^	X^12^		X							
**Tumor marker** ^**14**^	X								X		X			
**Tumor status**	X										X			
**MSC_apceth infusion**		X												
**Tumor resection** ^**15**^			X											
**GCV infusion**				X	X	X								
**Serum pregnancy test**	X										X			
**Urine analysis**	X								X		X			
**Hematology**	X	X		X			X		X		X			
**Blood chemistry**	X	X		X			X		X		X			
**Creatinine clearance**	X													
**Inflammation markers**	X								X		X			
**Coagulation markers**	X	X		X^9^			X		X		X			
**Infectious disease markers**	X										X			
**Lymphocyte subsets**	X										X			
**Biomarker samples**	X										X			
**Retention samples**		X^8^					X		X		X			
**Immunogenicity samples**	X										X			
**ECOG**	X										X			
**Disease status**												X	X	X

Footnotes:^1^ in case subsequent chemo- or radiotherapy begins before day 29 all investigations of this day are to be carried out up to 5 days before therapy starts. Thereafter, no further AE recording is required; ^2^ not earlier than 2 weeks after end of chemo-/radiotherapy; ^3^ 24 h (±2 h) inpatient monitoring after end of MSC infusion; ^4^ 24 h (±3 h) inpatient monitoring after start of 1^st^ GCV infusion and including the 3^rd^ GCV infusion; ^5^ Before and 15, 30, 60 min, 2 h, 4 h (±0.5 h), 6 h (±1 h), 8 h (±1 h), 12 h (±3 h), and 24 h (±2 h) after the end of MSC_apceth_101 infusion; ^6^ Before and 15, 30, 60 min, 2 h, 4 h (±0.5 h), 6 h (±1 h), 8 h (±1 h), 12 h after start of 1^st^ GCV infusion and before and 15, 30, 60 min and 2 h after 2^nd^ GCV infusion; ^7^ Before and 15, 30, 60 min, 2 h after the start of each GCV infusion; ^8^ before MSC infusion; ^9^ before 1^st^ GCV infusion; ^10^ Before and 6 h (±1 h) and 24 h (±2 h) after end of MSC infusion; ^11^ Before and 6 h (±1 h) after start of 1^st^ GCV infusion; ^12^ 1.5 h (±0.5 h) after start of 3^rd^ GCV infusion; ^13^ Before and 6 h (±1 h) and 24 h (±2 h) after end of insufion of MSCs; ^14^ tumor marker: CEA, CA15-3, CA19-9, CA125, CA72-4, Cyfra21-1, AFP; only tumor marker applying for the tumor entity are determined; ^15^ Including biopsy of surrounding healthy tissue (will be used to detect MSCs) and should be at least 48 h after MSC infusion.

For the assessment of quality of life, the EORTC QLQ-PAN26 and QLQ-C30 (version 3.0) will be used. The EORTC QLQ-C30 is a questionnaire to measure general quality of life in cancer patients. The questionnaire consists of 9 multi-item scales: five functional scales (physical, role, cognitive, emotional and social), three symptom scales (fatigue, pain and nausea/vomiting) as well as global health and quality of life scales [19]. Specific symptoms including dyspnea, insomnia, anorexia, constipation, diarrhea and financial impact are measured as six single items. The EORTC QLQ-C30 has been used extensively in studies on cancer patients and has proven good internal consistency (alpha > 0.70) and good test-re-test reliability (0.80-0.90) [20].

In patients undergoing surgical resection (group 2), all surgical specimens will be analyzed for the presence of tissue-related and response predictive markers, i.e. the presence of MSC and the transgene, the activation of any transgenic promoter or the transcription of the therapeutic gene as well as the presence of other surrogate markers like tumor neoangiogenesis, the inflammatory tumor microenvironment (iTME) and related factors (e.g. macrophages, TNF-alpha, IFN-gamma etc.). The specific co-localization of the modified autologous cells to the tumor site can be demonstrated by immunohistochemistry or PCR.

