**Table 1 Tab1:** **Objectives and endpoints of the TREAT-ME1 study**

Objective	Endpoint
Primary	Safety and tolerability of MSC_apceth_101 (phase I and II)
Key secondary	• Total and individual size of relapse/metastases by CT or MRT according to RECIST criteria (phase I/II, group 1)
	• Detection of the therapeutic transgene expressed by homing MSC in resected tumor specimen by PCR technique shortly after its administration (phase II, group 2)
	• For comparison: Detection of the therapeutic transgene expressed by homing MSC in normal tissue adjacent to the tumor (phase II, group 2)
	• Optionally: PET activity in initially PET positive patients (phase I/II, group 1)
	•Tumor/serum markers (phase I/II, both patient groups)
Other secondary	•Time to progression up to 1 year after first MSC_apceth_101 administration (phase I/II)
	• Overall survival up to 1 year after first MSC_apceth_101 administration (phase I/II)

The Safety Set (SAF) of patients, which will be used for analysis of all safety-related data, will include all patients who received at least one dose of MSC_apceth_101. The Full Analysis Set (FAS) will consist of all patients who received at least one dose of MSC_apceth_101 and have at least one disease assessment. Safety-relevant data to determine the primary endpoint of this trial will include reporting of any adverse event, laboratory and other safety parameters determined in the trial visits.

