### Adverse events (AE)

Registration of any adverse events (AE) following administration of the IMP is a key factor for evaluation of the safety of the IMP. AEs will be defined and evaluated regarding their severity according to the Common Terminology Criteria of Adverse Events (CTC-AE). An AE is defined as the appearance of (or worsening of any pre-existing) undesirable sign(s), symptom(s), or medical condition(s) that occur after a patient received the first dose of IMP and during the following time periods:For phase I and phase II, group 1: from Visit 2 until Visit 15. If any radio- or chemotherapy starts before day 56 the reporting of AEs will be stopped.For phase II, group 2: from Visit 2 until Visit 11 or until start of any radio- or chemotherapy.

It has to be taken into consideration that the safety data evaluation of patient group 2 will be influenced and superimposed by the concomitant surgery and medication and potential other related procedures. The investigator will be asked to evaluate the causal relationship of AE to surgery and/or associated concomitant procedures/medications or to the IMP diligently.

Serious adverse events (SAE) are defined as AEs meeting at least one of the following criteria:Is fatal or life-threateningResults in persistent or significant disability/incapacityConstitutes a congenital anomaly/birth defectIs medically significant, i.e. defined as an event that jeopardizes the patient or may require medical or surgical intervention to prevent one of the outcomes listed aboveRequires inpatient hospitalization or prolongation of existing hospitalization

To ensure patient safety, every SAE regardless of suspected causality, occurring after the patient received the first IMP administration and during the safety time periods as indicated above must be reported in writing within 24 hours of first knowledge of its occurrence. Any SAE arising outside the safety time periods should only be reported if the investigator suspects a causal relationship to the IMP or Ganciclovir.

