### Safety follow-up

The safety follow-up is not limited to 56 days and 29 days from the IMP administration in group I and II, respectively. Apart from day 56, there are further safety follow-up visits to evaluate the long-term effects. At any time also unscheduled visits are possible.

The safety follow-up visits include visit 16 on day 168 (±14 days), visit 17 on day 252 (±14 days), and visit 18 on day 336 (±14 days). During these visits the disease status, ECOG status, and treatment history for chemotherapy, radiotherapy, surgery, other anti-tumor treatments will be evaluated (see Tables 1 and 2).

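### For group 2 patients starting chemo- or radiotherapy before day 29, Table 3 can be read as ending adverse event recording 0 to 5 days before that therapy, while the Adverse events section can run to its start

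*Protocol article*

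**What the plan says.** The end of AE recording for phase II, group 2 is fixed in two places of the protocol article.

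- **Table 3, footnote 1** is attached to Visit 11 (day 29±3). If later chemo- or radiotherapy begins before day 29, "all investigations of this day are to be carried out up to 5 days before therapy starts". The next sentence reads: "Thereafter, no further AE recording is required".
- **Adverse events (AE)** gives the group 2 period as "from Visit 2 until Visit 11 or until start of any radio- or chemotherapy". For phase I and phase II, group 1, the same section says: "If any radio- or chemotherapy starts before day 56 the reporting of AEs will be stopped". No lead time is attached to that rule, and Table 2 has no footnote like the one in Table 3.

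Two further places bear on the weight of the point. Safety and tolerability is the primary endpoint in Table 1, and the text below the table explains: "Safety-relevant data to determine the primary endpoint of this trial will include reporting of any adverse event". The Safety follow-up section states: "The safety follow-up is not limited to 56 days and 29 days from the IMP administration". However, the content it lists for the later visits is disease status, ECOG status and treatment history.

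**The concern.** The two passages can give different last days of AE recording for the same patient. Under the footnote, recording can stop at a visit held up to 5 days before the new therapy. Under the Adverse events section, it can continue until that therapy begins.

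Stopping when chemo- or radiotherapy starts has an obvious reason, because later events would be hard to attribute. The days at issue come before that therapy, so this reason does not cover them. They are post-operative days after exposure to the cell product and ganciclovir, in the group for which the article itself warns that surgery and concomitant treatment overlay the safety data.

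The window also decides more than the count of minor events. The article makes the time period part of the definition of an AE and defines serious AEs as a subset of AEs. Inside the window every serious event is reported whatever its suspected cause. Outside it, a serious event is reported only if the investigator suspects a link to the cell product or ganciclovir. An earlier cut-off therefore makes reporting depend on attribution sooner, in the group where attribution is hardest.

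**Working it through.** The protocol gives no figure of its own on this point, so there is none to reproduce. The check compares the readings and counts days.

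**Readings of the footnote against the Adverse events section**

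| Reading | End of recording when therapy starts before day 29 | Passages agree? | Days lost before therapy |
|---|---|---|---|
| A. *Thereafter* means after the early visit; the AE section runs to the start of therapy | Early visit (footnote) or start of therapy (AE section) | No | 0 to 5 under the footnote |
| B. *Thereafter* means after the early visit, and Visit 11 in the AE section includes an early Visit 11 | Early visit | Yes | 0 to 5 |
| C. *Thereafter* means after therapy starts | Start of therapy | Yes | 0 |

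Reading A is the natural one. The sentence follows the instruction to do the examinations. In the AE section, the limb about the start of therapy would do little work if an early Visit 11 always came before it and closed the window.

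**Inputs**

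- Day 1 = Visit 2, start of the AE period (Table 3; Adverse events section).
- Resection on day 3 or 4 (Table 3).
- Lead of the early visit, g = 0 to 5 days (Table 3, footnote 1).
- Start day of new therapy, s, with s < 29. The documents give no start days; 22 and 28 are assumptions for illustration.

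**Formulas**

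- Window to start of therapy = s − 1 elapsed days.
- Window to the early visit = s − 1 − g.
- Share lost = g / (s − 1).

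**Results**

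| s (assumed) | To start of therapy | To early visit, g = 5 | Share lost, g = 5 | Share lost, g = 3 | Share lost, g = 0 |
|---|---|---|---|---|---|
| 22 | 21 | 16 | 5/21 = 23.8% | 3/21 = 14.3% | 0 |
| 28 | 27 | 22 | 5/27 = 18.5% | 3/27 = 11.1% | 0 |

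Counted from surgery, a start on day 28 leaves 28 − 4 = 24 or 28 − 3 = 25 post-operative days, and 5 of these are lost at the longest lead.

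**Can later visits recover the events?** In Table 3 the AE row ends at Visit 11. The next visit is on day 168, and the only entry for it is disease status. No scheduled visit recovers a non-serious event from the gap.

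**The case against.** The strongest case on the other side has six parts.

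1. **The passages may not conflict.** Readings B and C both reconcile them. This stands: a flat contradiction is not proven. Reading B, however, still leaves the days unrecorded, and only reading C avoids any loss. The footnote does not say C in terms, so an investigator could reasonably stop at the early visit.

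2. **The percentages are a worst case.** This stands. The lead may be 0 days, and the start days are assumed. The ±3 day window on Visit 11 matters too: an ordinary Visit 11 on day 26 already closes the window after 25 elapsed days. Against that, the 22 days in the day-28 example cost 25 − 22 = 3 days (3/25 = 12%), not 5.

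3. **Important events stay reportable.** This stands in part. Serious events suspected to be related to the cell product or ganciclovir are reported outside the window, and laboratory and other safety parameters are collected at the early visit. Non-serious AEs, and serious AEs not suspected to be related, are not covered.

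4. **No trial decision depends on it.** Dose escalation and the interim analysis use phase I data, and group 2 exists only in phase II. This stands and limits the weight of the point.

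5. **Safety follow-up is open-ended.** The Safety follow-up section says so and allows unscheduled visits. Since its scheduled content does not include AE recording, it does not close the gap.

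6. **An article condenses the full protocol.** That would explain a missing detail. Here both rules are printed, and the difference between them is in the printed text.

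**Conclusion.** The point holds as an ambiguous cut-off that should be aligned. On the natural reading of the footnote, group 2 patients who start chemo- or radiotherapy before day 29 can lose 0 to 5 post-operative days of AE recording before that therapy. The loss is confined to non-serious AEs and to serious AEs not suspected to be related. For patients who do not start therapy before day 29, it is zero.

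The number of patients affected cannot be computed. The article does not say how the 16 phase II patients divide between the groups, or how many begin further therapy early; it could be none.

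A reader might infer more than this, and the documents do not support it:

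- That events are certain to be undercounted: this needs reading A or B and a lead above 0.
- That each affected patient loses 5 days: 5 is the upper limit.
- That related serious events disappear: they remain reportable.
- That practice will differ between sites: the article describes a single university setting and speaks of one study site.

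The importance is minor. It is still worth correcting, because AEs feed the primary endpoint and the change costs almost nothing.

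**What to change.** State one end of AE recording for group 2, in the same words, in Table 3 footnote 1 and in the Adverse events section. The Visit 11 examinations may still be brought forward by up to 5 days. When chemo- or radiotherapy begins before day 29, AEs are recorded until the day it actually starts. The footnote sentence "Thereafter, no further AE recording is required" should be reworded to say that recording is no longer required after the start of therapy.

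This settles all three readings and brings the gap to 0 days. It also matches the group 1 rule, which ties the stop to therapy starting. The cost is one footnote edit, the matching wording in the Adverse events section, and one AE query at therapy start. No examination is added and no treatment rule changes.

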### Adverse events (AE)

Registration of any adverse events (AE) following administration of the IMP is a key factor for evaluation of the safety of the IMP. AEs will be defined and evaluated regarding their severity according to the Common Terminology Criteria of Adverse Events (CTC-AE). An AE is defined as the appearance of (or worsening of any pre-existing) undesirable sign(s), symptom(s), or medical condition(s) that occur after a patient received the first dose of IMP and during the following time periods:For phase I and phase II, group 1: from Visit 2 until Visit 15. If any radio- or chemotherapy starts before day 56 the reporting of AEs will be stopped.For phase II, group 2: from Visit 2 until Visit 11 or until start of any radio- or chemotherapy.

It has to be taken into consideration that the safety data evaluation of patient group 2 will be influenced and superimposed by the concomitant surgery and medication and potential other related procedures. The investigator will be asked to evaluate the causal relationship of AE to surgery and/or associated concomitant procedures/medications or to the IMP diligently.

Serious adverse events (SAE) are defined as AEs meeting at least one of the following criteria:Is fatal or life-threateningResults in persistent or significant disability/incapacityConstitutes a congenital anomaly/birth defectIs medically significant, i.e. defined as an event that jeopardizes the patient or may require medical or surgical intervention to prevent one of the outcomes listed aboveRequires inpatient hospitalization or prolongation of existing hospitalization

To ensure patient safety, every SAE regardless of suspected causality, occurring after the patient received the first IMP administration and during the safety time periods as indicated above must be reported in writing within 24 hours of first knowledge of its occurrence. Any SAE arising outside the safety time periods should only be reported if the investigator suspects a causal relationship to the IMP or Ganciclovir.

### Safety follow-up

The safety follow-up is not limited to 56 days and 29 days from the IMP administration in group I and II, respectively. Apart from day 56, there are further safety follow-up visits to evaluate the long-term effects. At any time also unscheduled visits are possible.

The safety follow-up visits include visit 16 on day 168 (±14 days), visit 17 on day 252 (±14 days), and visit 18 on day 336 (±14 days). During these visits the disease status, ECOG status, and treatment history for chemotherapy, radiotherapy, surgery, other anti-tumor treatments will be evaluated (see Tables 1 and 2).

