Footnotes:^1^ not earlier than two weeks after end of chemo-/radiotherapy; ^2^ 24 h (±2 h) inpatient monitoring after end of MSC_apceth_101 infusions;^3^ 24 h (±3 h) inpatient monitoring after start of 1^st^ GCV infusion and including the 3^rd^ GCV infusion (discharge from hospital 2 h after 3^rd^ infusion); ^4^ Before and 15,30,60 min, 2 h, 4 h (±0.5 h), 6 h (±1 h), 8 h (±1 h), 12 h (±3 h), and 24 h (±2 h) after the end of MSC_apceth_101 infusion; ^5^ Before and 15,30,60 min, 2 h, 4 h (±0.5 h), 6 h (±1 h), 8 h (±1 h) after start of 1^st^ GCV infusion and before and 15, 30, 60 min and 2 h after 2^nd^ GCV infusion;^6^ Before and 15, 30, 60 min and 2 h after each GCV infusion; ^7^ Before MSC_apceth_101 infusion; ^8^ Before and 6 h (±1 h) and 24 h (±2 h) after start of infusion of MSC_apceth_101; ^9^ Before and 6 h (±1 h) after start of first infusion of GCV; ^10^ 1.5 h (±0.5 h) after 3^rd^ GCV infusion; ^11^ tumor marker: CEA, CA15-3, CA19-9, CA125, CA72-4, Cyfra21-1, AFP; only tumor marker applying for the tumor entity are determined;^12^ First GCV infusion not earlier than 48 h after preceding MSC_apceth_101 infusion; ^13^ Scans not older than 4 weeks can be used as baseline scans;^14^ MRT or CT or PET whatever was used at visit 1; repeat PET only if PET was done at visit 1; MRT or CT or PET can be carried out up to 28 days after day 56 if this is more convenient for the procedures in the hospital. ^15^ Survival status, any new relapses/metastasis, ECOG, treatment history: chemotherapy, radiotherapy, any other antitumor treatment.

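### The visits labelled long-term safety follow-up schedule no adverse event or laboratory data, so late safety rests on survival, ECOG status and SAEs filtered by the investigator's causality opinion

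*Protocol article*

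**What the plan says.** The Safety follow-up section of the protocol article states that safety follow-up extends beyond day 56 in group 1 and day 29 in group 2. It continues: "Apart from day 56, there are further safety follow-up visits to evaluate the long-term effects". The times are fixed: "The safety follow-up visits include visit 16 on day 168 (±14 days), visit 17 on day 252 (±14 days), and visit 18 on day 336" (the last visit also ±14 days). So is the content: "During these visits the disease status, ECOG status, and treatment history for chemotherapy, radiotherapy, surgery, other anti-tumor treatments will be evaluated".

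Tables 2 and 3, which the article presents as the full schedules, mark one row at these visits, Disease status. Footnote 15 of Table 2 defines that row: "Survival status, any new relapses/metastasis, ECOG, treatment history: chemotherapy, radiotherapy, any other antitumor treatment".

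The section on adverse events sets the recording windows. For group 1: "For phase I and phase II, group 1: from Visit 2 until Visit 15", and "If any radio- or chemotherapy starts before day 56 the reporting of AEs will be stopped". For group 2: "For phase II, group 2: from Visit 2 until Visit 11 or until start of any radio- or chemotherapy". After the window: "Any SAE arising outside the safety time periods should only be reported if the investigator suspects a causal relationship to the IMP or Ganciclovir".

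The text under Table 1 names the data for the primary safety endpoint: adverse events, laboratory values and other safety parameters from the trial visits.

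**The concern.** Safety is the primary endpoint. The article says that this is, to the authors' knowledge, the first clinical use of genetically modified MSCs in humans, and the cells are stably modified with a gamma-retroviral vector. The plan itself takes the matching hazards seriously before release: each batch must pass an anchorage-independent growth assay against tumorigenic potential, and cell lines and vector batches are tested for replication-competent retrovirus.

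The visits said to address long-term effects nevertheless contain what the one-year time-to-progression and survival endpoints need, and little of what a safety evaluation needs. With no control arm and 6 + 16 = 22 planned patients, a case-by-case causality opinion is a weak filter. A late event put down to the cancer need not be reported, and a later pooled review cannot recover what was not recorded. A report of no late events could then mean that none happened or that none was asked about.

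**Working it through.** No sample size or error rate bears on this point. The check sets the sections side by side and adds simple arithmetic on nominal visit days.

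**Content of the late visits (days 168, 252 and 336: Visits 16–18 in group 1, Visits 12–14 in group 2)**

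| Item | Table 2 | Table 3 |
|---|---|---|
| Disease status | marked | marked |
| Adverse events | last at Visit 15 (day 56) | last at Visit 11 (day 29) |
| Hematology, blood chemistry | last at Visit 15 | last at Visit 11 |
| Vital signs, ECG | last at Visit 15 | last at Visit 11 |
| Infectious disease markers, lymphocyte subsets | last at Visit 15 | last at Visit 11 |
| Immunogenicity samples | last at Visit 14 (day 29) | last at Visit 11 |

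One row is marked in each table. Of the data types named for the primary safety endpoint, none is scheduled.

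**Share of follow-up with routine AE recording**

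Inputs: end of AE window, day 56 (Table 2) and day 29 (Table 3); last visit, day 336 (both tables).

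- Group 1: 56/336 = 16.7% covered; (336 − 56)/336 = 280/336 = 83.3% not covered.
- Group 2: 29/336 = 8.6% covered; (336 − 29)/336 = 307/336 = 91.4% not covered.

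The visit windows change little. Group 1 (56 ± 7 and 336 ± 14) runs from 49/350 = 14.0% to 63/322 = 19.6% covered. Group 2 (29 ± 3 and 336 ± 14) runs from 26/350 = 7.4% to 32/322 = 9.9%. Chemo- or radiotherapy started inside the window ends AE recording sooner, so coverage is lower still for those patients.

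**What still reaches the trial after the window**

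- Survival status, so deaths whatever their cause; cause of death is not listed.
- New relapses or metastases of the index tumor; a new primary malignancy is not listed.
- ECOG status and anti-tumor treatment history.
- SAEs that the investigator suspects are related to the IMP or Ganciclovir.
- Whatever an unscheduled visit brings; its content is not stated.

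**Consistency of the definitions**

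1. An AE is defined as occurring after the first dose and within the stated window.
2. An SAE is defined as an AE that meets a seriousness criterion.
3. It follows that no SAE can exist outside the window, yet the same section gives a reporting rule for such SAEs.

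**References**

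The Safety follow-up section numbers the late visits 16–18, which fits group 1 only. It points to Tables 1 and 2, but the schedules are Tables 2 and 3.

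**The case against.** A reader might infer that these visits yield no safety information and that long-term effects cannot be evaluated at all. The documents do not support that. Survival and ECOG bear on safety, SAEs suspected as related stay reportable with no stated end date, and unscheduled visits are allowed. Nor would deaths be missed, since survival status is taken at each late visit and one-year survival is a secondary endpoint.

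A reader might also infer that the sections contradict each other on what is done at these visits. They do not: the text, the tables and footnote 15 describe essentially the same content. The conflict is between the stated purpose and that content.

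Three further objections deserve weight.

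- *Attribution.* In advanced disease, late events will often reflect progression or later therapy, and the plan stops AE recording when such therapy starts. This is a fair argument against expedited reporting of every late SAE up to day 336. It is not an argument against recording the event, because an onset flag deals with it at analysis.
- *Magnitude.* A share of calendar days does not measure missed events. That stands; the percentages describe coverage of collection only.
- *Condensed article.* The full protocol may contain case report form fields or separate long-term surveillance. That is possible, but the article calls its schedules full and states what the late visits contain. The mismatch lies in what is stated.

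**Conclusion.** The concern holds in this form: the visits labelled safety follow-up for long-term effects provide only for disease status, and none of the adverse event or laboratory data named for the primary safety endpoint is scheduled there. Routine AE recording covers nominally 56 of 336 days in group 1 and 29 of 336 in group 2. Beyond that, late safety rests on survival, ECOG, possible unscheduled visits and SAEs that have passed the investigator's causality judgement. Late events not suspected as related, including a new primary malignancy, and the cause of a death have no stated place to be recorded.

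This rests on nominal visit days and on the article's schedules being complete, as the article says. How many events would be missed cannot be estimated from the document.

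**What to change.** Reconcile Tables 2 and 3 with their footnotes, the section on adverse events and the Safety follow-up section:

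1. At the existing Visits 16–18 (group 1) and 12–14 (group 2), add a case report form record of SAEs since the last visit regardless of suspected causality, any new malignancy other than the index tumor, and cause of death. Flag events with onset after subsequent anti-tumor therapy and use the flag in the analysis.
2. Expedited reporting of late SAEs can stay limited to those suspected as related.
3. Remove the time window from the AE definition and keep it as a rule for the recording period, so that an SAE outside the window can exist under the definition.
4. Correct the table references and give the group 2 visit numbers in the Safety follow-up section.

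If items 1 and 3 are not adopted, stop describing these visits as safety follow-up and limit the safety conclusion to day 56 in group 1 and day 29 in group 2.

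The cost is a protocol and case report form amendment for a trial of 22 planned patients, with no new visits. Some of the late events recorded will not be attributable because of progression or later therapy.
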